### Measurements

#### Schedule, Sociodemographic Data, and Social Support

Clinical research assistants will conduct all assessments at baseline and at weeks 6, 12, and 24 after consent, in person, over the phone, or using telemedicine. Data will be stored in REDCap (Research Electronic Data Capture), a secure, web-based software platform designed to support data capture for research studies [53,54] (see Figure 2 for assessment and procedure schedule corresponding to the Standard Protocol Items: Recommendations for Interventional Trials [SPIRIT] statement [55]). Sociodemographic data will be collected at baseline and will include gender identity, biological sex, ethnicity, educational attainment, employment or studying status, income, living arrangements status, and housing status. To measure social support, we will use the 10-item Social Provisions Scale, which has been validated in individuals with schizophrenia and includes 5 domains: tangible help, emotional support or attachment, orientation, reassurance of worth, and social integration [56]. Items will be measured on a 4-point Likert scale from “1-totally disagree” to “4-totally agree,” and higher total scores (range 10-40) indicate better social support.

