#### Secondary Outcomes

The secondary outcomes are as follows:

Cannabis use will be measured using a self-report tool, the Timeline Follow Back (TLFB) [57]. On the basis of the TLFB, for each day in the last 14 days, participants indicate first if they used cannabis (yes or no). To facilitate their recollection, participants will be asked about memorable days (eg, birthdays) and patterns of use (eg, more use on weekends). Then, for each day they used cannabis, they will provide the quantity of cannabis used. Participants will be reasked about the cannabis form used (dried cannabis smoked, oral spray, oral oil, dried cannabis vaporized, concentrated vapor, oral capsules, beverages, edibles, etc) and for each form, they will provide the quantity and the unit (eg, g, mg, and mL) and the concentration in tetrahydrocannabinol and cannabidiol (%, mg/mL, mg/dose, or unknown). The quantity of cannabis used on a specific day represents grams per method of cannabis use (eg, dried cannabis smoked) × number of times the method is used per day. The quantity of cannabis used in the last 14 days will be calculated. The inclusion of the quantity of cannabis use as a secondary outcome, which has been used in other similar trials [35], is justified by research suggesting that in individuals with psychosis and CUD, face-to-face psychological interventions (MI and CBT) are more effective in decreasing the quantity than the frequency of use [22].Participant satisfaction with using iCC or programs for CUD offered as part of EIS (control group) will be measured with the validated 8-item Client Satisfaction Questionnaire (CSQ-8) [58]. Items (eg, “How would you rate the quality of program you received”) are scored on a scale from 1 to 4 and a higher total score reflects higher satisfaction. Participants who discontinue participation in the study will be invited to complete the CSQ-8 upon discontinuation. Other details about their experiences are collected in an open-ended format.App use: Considering the importance of evaluating app use and adoption metrics in eHealth trials [43], data will be collected automatically through iCC for the entire 24-week participation in the intervention. The following outcomes will be monitored: number of iCC modules and strategies completed, number of times a particular module was opened and completed, time spent on individual iCC modules, time elapsed between the initiation and completion of individual iCC modules, and total time spent completing the iCC intervention and boosters. For each participant, iCC data will be synchronized with a password-protected Amazon Web Services account for a period of 24 weeks. Data related to clinicians’ use of the dashboard (ie, number of logins) are synchronized with the Amazon Web Services account and will be used for exploratory analyses of clinician involvement in monitoring participant progress during the intervention.Trial parameters: Information collected during enrollment and study visits (stored in REDCap) will allow us to calculate the number of participants who were referred to the study, screened, eligible, provided informed consent, randomized, initiated the intervention (ie, who both logged into iCC and complete module 1), and completed baseline and follow-up assessments.

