
#### Exploratory Outcomes

The exploratory outcomes are as follows:

Cannabis use frequency (and abstinence) will be measured using the TLFB. Participants who declare using alcohol will be asked about the frequency and quantity of use, and those who consume other substances (eg, cocaine, amphetamine, opioids) will be asked about the frequency of use and route of administration.Cannabis-related negative social, occupational, physical, and personal consequences will be assessed using the 19-item unidimensional self-report instrument, the Marijuana Problems Scale (MPS) [59,60]. Higher MPS scores (range 0-38) denote more negative cannabis use consequences.Cannabis use disorder severity will be measured with the 5-item Severity of Dependence Scale (SDS), which has been validated in people with early psychosis [61,62]. Higher total scores (range 0-15) indicate more severe dependence symptoms.Confidence in resisting cannabis use in 8 different situations (eg, “if other people treated me unfairly or interfered with my plans”) will be measured using the validated Drug-Taking Confidence Questionnaire (DTCQ) [63], with higher scores denoting higher confidence levels to resist cannabis use.The measurement of intentions to stop using cannabis has been informed by and adapted from the Precaution Adoption Process Model [64], a theoretical stage-based model that allows participants to place themselves in one of 6 nominal stages: (1) unengaged (ie, “As of right now, I haven’t thought about if I want to stop using cannabis”); (2) undecided (ie, “I’m still unsure if I want to stop”); (3) decided not to act (ie, “I do not want to stop”); (4) decided to act (ie, “I want to stop”); (5) acting (ie, “I recently stopped”); and (6) maintenance (ie, “I stopped using cannabis over a month ago”).The severity of positive and negative symptoms of psychosis will be measured using an interviewer-administered scale, the Positive and Negative Syndrome Scale (PANSS-6) [65]. This well-validated short version of the PANSS has been chosen rather than the complete 30-item version to reduce the burden of data collection. A total score of 6 reveals no psychotic symptoms, and a total score of <14 will be considered the cutoff for remission of schizophrenia [65].To measure cannabis-related harm, we will use the 17-item Protective Behavioral Strategies-Marijuana (PBSM) questionnaire, which has been shown to be valid and free of bias in terms of gender, sex, race, ethnicity, and recreational marijuana use legal status [66]. We use the table provided by Pedersen et al [66] to convert the sum score into Item Response Theory scale scores, with higher scores indicating higher-risk behaviors [66].Participants will report their Satisfaction with Life pertaining to 4 domains (ie, living situation, social relationships, work, self, and present life) using the 18-item Satisfaction with Life questionnaire (SWL), which has been validated for schizophrenia and schizophrenia-related disorders [67]. In each domain, higher mean scores indicate greater satisfaction.Self-reported health service use data using the Health Care form will include emergency department visits and hospitalizations for psychological, emotional, or mental health issues in the last 30 days (yes or no). In the case of hospitalization, additional data will be collected (ie, number of admissions, duration of stay, reason for admission, and confirmation using medical records).

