### Statistical Analyses

The 1-sided chi-square 95% CI will be calculated to estimate the lower bound of iCC completion and trial retention rates. We will consider participation in iCC acceptable if more than 50% of the participants completed at least 11 out of 21 intervention modules at week 12. The trial will be considered feasible if the attrition at week 12 does not reach 50%. An analysis of covariance model will be used to provide a preliminary assessment of the effect of treatment on the quantity of cannabis use (dependent variable) at 12 weeks (end of intervention). The independent variables will be the quantity of cannabis use at baseline and a dichotomous variable reflecting arm allocation. The second model will include covariates that were found to be different between the groups at baseline. For participants’ satisfaction with the intervention, we will calculate the CSQ total scores as well as the mean and SD. The groups will be compared using a mixed-effects model with random intercepts for each site. For app use and trial parameters, we will use univariate analyses and report the distribution (frequency tables), central tendency (mean, median, and mode), and dispersion (range and SD).

For exploratory outcomes, we will compute descriptive statistics and bivariate and multivariable analyses using generalized estimating equation (GEE) models. The generalized estimating equation is a repeated-measures regression model that accounts for the correlations between repeated measures for each person [70]. We will use different types of GEE modeling depending on the distribution of the outcome. For cannabis frequency (count data), we will use Poisson; for the abstinence (binary), we will use binomial; and for continuous variables (ie, scores calculated for MPS, SDS, DTCQ, PANSS, PBSM, SWL, and SPS), we will use linear GEE modeling. Using this analytic approach, we will estimate the multivariable associations between the outcomes and study visits (ie, baseline and end of intervention), study condition (the reference group will be the control arm), and their interaction, as well as other predictors and covariates, such as sociodemographics, social support, CUD severity, behavioral stage of change, medication status, and other substance use. We will use the chi-square test of proportions to compare behavioral stages at different time points and between the 2 study arms.

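### Change in behavioral stage over time is to be tested with an independent-samples chi-square although the same participants answer at each visit; the test is conservative and loses power

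*Protocol article*

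**What the plan says.** Statistical Analyses gives one sentence to the stage outcome: "We will use the chi-square test of proportions to compare behavioral stages at different time points and between the 2 study arms".

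The outcome is defined under Exploratory Outcomes. An adapted stage model "allows participants to place themselves in one of 6 nominal stages", from not having thought about stopping to having stopped more than a month ago. Under Schedule, Sociodemographic Data, and Social Support: "Clinical research assistants will conduct all assessments at baseline and at weeks 6, 12, and 24 after consent". Each participant can therefore contribute a stage at several visits.

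The same paragraph of Statistical Analyses describes GEE as "a repeated-measures regression model that accounts for the correlations between repeated measures for each person". It assigns GEE to use frequency, abstinence and the scale scores, but not to the stages. On frequency it says: "For cannabis frequency (count data), we will use Poisson". Under Exploratory Outcomes, "Cannabis use frequency (and abstinence) will be measured using the TLFB", and the Timeline Follow Back is described under Secondary Outcomes as a record in which, "for each day in the last 14 days, participants indicate first if they used cannabis (yes or no").

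**The concern.** On its natural reading the sentence on stages covers two comparisons, between time points and between arms. The second involves different people. The first involves the same people twice. The chi-square test computes its standard error as if the two sets of answers were unrelated. When a person's answers are positively correlated, the true variance of the change is smaller than the test assumes, so it rejects too rarely.

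The result would not be a false claim of benefit. The risk is that a real change in intention is reported as no change. Motivation to change is one of the exploratory outcomes that Study Objectives names as a means of understanding the benefit of the app.

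**Working it through.** **The plan's own figure.** The article gives no calculation for the stage analysis. Its only sample-size figure, for the primary outcomes, reproduces: (1.645 + 0.842)² × 0.7 × 0.3 / 0.2² = 32.5, so 33 per arm, and 2 × 33 / 0.7 = 94. It does not bear on this point.

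**Inputs.**
- From the article: about 100 participants and an expected maximum attrition of 30% by week 12, hence 100 × 0.7 = 70 pairs; six nominal stages.
- Assumed, because the documents give neither: the within-person correlation and the stage shares. The six-stage simulation uses shares of 15%, 30%, 15%, 30%, 6% and 4% at both visits. All tests are at a nominal two-sided 5%.

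**Six stages, as planned.** Paired stages were simulated from a bivariate normal with latent correlation rho and identical margins, so that no change is true. They were then tested with the independent-samples chi-square.

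| Latent rho | True level, 70 pairs |
|---|---|
| 0 | about 4.3% |
| 0.3 | about 3.5% |
| 0.5 | about 2.3% |
| 0.7 | about 1.4% |

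Repeated runs differ by a few tenths of a percentage point.

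**Two stages, if collapsed.** Let phi be the correlation between the two binary answers. With equal margins p, the variance of the change is 2p(1−p)(1−phi)/n, while the chi-square uses 2p(1−p)/n. The true level is therefore 2 × [1 − Φ(1.96/√(1−phi))]:
- phi 0.3: 1.96/0.837 = 2.34, level 1.9%
- phi 0.5: 1.96/0.707 = 2.77, level 0.6%
- phi 0.7: 1.96/0.548 = 3.58, level 0.03% (0.04% by simulation)

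**Power for a shift from 40% to 55%, two stages, 70 pairs (simulated, 40,000 replicates).**

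| phi | Chi-square | McNemar | Difference |
|---|---|---|---|
| 0.3 | 42% | 58% | 16 points |
| 0.5 | 40% | 72% | 32 points |
| 0.7 | 37% | 94% | 57 points |

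Latent rho and phi are different scales. For an even split, latent 0.5 corresponds to phi 0.33 and latent 0.7 to phi 0.49, so the two sets of levels should not be read against each other at the same nominal value.

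**Between arms at one visit.** With independent samples and the same six stage shares, the chi-square has a level of 3.7% at 35 per arm and 4.5% at 50 per arm. That half of the sentence is sound.

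**Use days.** Fourteen yes/no answers give a count from 0 to 14. A Poisson distribution has no ceiling: with means of 10, 11 and 12 days (assumed) it puts 8%, 15% and 23% of its mass above 14. In simulated 0–14 data with two visits and no arm-by-visit effect, Poisson GEE with robust standard errors had a level of 4.3% to 6.3%, and binomial GEE 5.0% to 6.5%. Only model-based standard errors with the scale fixed at 1 went wrong, at 0.5% to 34.8%.

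**The case against.** **The sentence may mean something else.** It can be read as comparing the arms at each time point, which involves no pairing. That is possible, but the wording joins the two comparisons with an "and", so the paired reading is the natural one. If the other was meant, no test of change in stage is specified and the sentence needs clarifying.

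**The largest figures are not for the planned analysis.** This stands. Levels below 1% arise only after collapsing to two stages and with phi of 0.5 or more. With six stages the loss is milder.

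**The outcome is exploratory and the error conservative.** This also stands. Limitations in the Discussion already promises cautious reading of efficacy data.

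**Stronger readings that the documents do not support.**
- A reader might infer that the Poisson model ignores repeated measurement or gives wrong error rates. It sits inside a GEE that the article says handles within-person correlation, and with robust variance it holds about 5%. The article does not state the variance estimator, a detail commonly left to the full plan.
- A reader might infer that the six-by-two table is too sparse to test. About 35 retained per arm over six stages averages 5.8 per cell; no stage distribution is given, and the simulated between-arm level was acceptable.
- A reader might infer that the last stage must be empty at baseline because entry requires use in the past month. Study Design allows 14 days for screening and a further 14 for the baseline assessments, so someone could pass a month without use before answering.

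**Conclusion.** The point holds for the comparison of stages between time points. As written, an independent-samples test is applied to paired answers, and its error rate is wrong in the conservative direction. The size rests on the assumed correlations and stage shares, and on 70 pairs. Under these, the loss runs from modest with six stages to substantial with a two-stage collapse and strongly correlated answers.

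The between-arm chi-square at a single visit is valid. The Poisson choice for use days is a secondary matter of fit, not of error rates, provided robust standard errors are used. The consequences stay within exploratory outcomes.

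**What to change.** For change in stage over time, name a paired method in place of the chi-square. Stuart-Maxwell keeps all six stages. Alternatives are McNemar on a prespecified collapse (for example, decided to act or beyond, yes or no), or that binary variable in the binomial GEE framework already planned, with arm, visit and their interaction. Keep the chi-square for comparing arms at one visit. If that was the only comparison intended, reword the sentence to say so.

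Optionally, model use days with a binomial GEE out of 14 days, logit link and robust standard errors, instead of Poisson.

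The cost is a change of wording in the analysis plan, with no new data and no change to the sample size. Collapsing the stages loses detail between them; the full six-stage distribution can still be reported descriptively.

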Missing entries for fields where missing values account for <5% of the sample may be imputed using the sample mean for continuous variables and sample mode for categorical variables. Fields with >5% missing entries may be excluded from multivariate models. In the case of missing visits, the proposed types of analyses (linear mixed-effects models and GEE models) will include all participants with at least one nonmissing visit, which may increase statistical power and reduce estimation bias. Our analysis plan includes both intention-to-treat and per-protocol analyses.

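### The week-12 ANCOVA of cannabis quantity is a completers' analysis that the plan's missing-visit statement does not cover

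*Protocol article*

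**What the plan says.** All of this stands in the protocol article under Statistical Analyses.

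- **Quantity of cannabis use (secondary outcome):** "An analysis of covariance model will be used to provide a preliminary assessment of the effect of treatment on the quantity of cannabis use" at 12 weeks. Its terms are few: "The independent variables will be the quantity of cannabis use at baseline and a dichotomous variable reflecting arm allocation". A second model adds covariates that differ at baseline. Week 6 appears in neither.
- **Satisfaction (secondary outcome):** "The groups will be compared using a mixed-effects model with random intercepts for each site". This is the only mixed model specified.
- **Exploratory outcomes:** GEE, for example "For cannabis frequency (count data), we will use Poisson; for the abstinence (binary), we will use binomial". The stated aim is to "estimate the multivariable associations between the outcomes and study visits (ie, baseline and end of intervention"), so week 6 is absent here as well.
- **Missing visits:** "the proposed types of analyses (linear mixed-effects models and GEE models) will include all participants with at least one nonmissing visit".
- **Missing fields:** optional mean or mode imputation below 5% missing; above that, "Fields with >5% missing entries may be excluded from multivariate models".
- **Analysis sets:** "Our analysis plan includes both intention-to-treat and per-protocol analyses".

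The Measurements section schedules all assessments at baseline and weeks 6, 12 and 24. The Sample Size section takes 30% as the maximum attrition expected at week 12; the Discussion expects a figure near 30%.

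**The concern.** The missing-visit statement names two model types and credits them with keeping partly observed participants and reducing bias. The quantity outcome is analysed by a third type, which keeps only those seen at week 12. A reader would reasonably take the reassurance, together with the intention-to-treat statement, to cover the trial's preliminary effect estimate. It does not.

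That estimate is one of the things the pilot hands on to a larger efficacy trial. Arm-dependent dropout is plausible here. The trial is open-label, every participant was selected for openness to an app, and controls may receive the app only after the end-point assessment, so reasons for staying until week 12 differ by arm. Data that could reduce any resulting bias are already to be collected at week 6.

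**Working it through.** **1. Which model covers which outcome**

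| Outcome | Model stated | Named in the missing-visit statement? | Week 6 used? |
|---|---|---|---|
| Quantity of cannabis | ANCOVA at week 12 | No | No |
| Satisfaction | Mixed model, site intercept | Yes, but no participant-level repeated measures are described | Not stated |
| Frequency, abstinence, scale scores | GEE | Yes | No; baseline and end of intervention only |

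For the GEE outcomes, someone lost before week 12 contributes a baseline value and no post-baseline value, so being included adds little about the treatment effect.

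**2. The plan's own sample size.** Inputs: 50% v 70%, one-sided 5%, 80% power.
(1.645 + 0.842)² × 0.7 × 0.3 / 0.2² = 32.46, so 33 per arm. Then 2 × 33 / 0.7 = 94.3, stated as 94 and rounded to about 100. Both figures reproduce. The 30% attrition is therefore the plan's own allowance.

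**3. Who enters the ANCOVA**
- N = 100, 30% attrition: 100 × 0.7 = 70 analysed, 30 left out.
- N = 94: 94 × 0.7 = 65.8, about 66 analysed and 28 left out.
- Just below the 50% feasibility limit, up to 49 of 100 could be left out.

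**4. Precision.** 95% half-width on a standardized difference, without the gain from baseline adjustment: 1.96 × √(2/50) = 0.39 SD with 50 per arm, and 1.96 × √(2/35) = 0.47 SD with 35 per arm. Power for the cited d = 0.19 (two-sided 5%) is 16% and 12%. The trial is not powered for this outcome either way.

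**5. Possible bias (simulation).** 50 per arm, no true effect, about 30% missing at week 12, 4,000 replicates per scenario, Monte Carlo error about 0.2/√4000 = 0.003 SD. The documents give no correlations or dropout mechanism, so these are assumptions. Correlations for baseline–week 6, baseline–week 12 and week 6–week 12 are 0.6/0.5/0.7 (set A) or 0.6/0.54/0.75 (set B). Slopes are log-odds of dropout per SD of use. The comparator is the likelihood estimate using baseline and week 6. A negative bias looks like a benefit of the app.

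| Dropout depends on | ANCOVA bias (SD) | Using week 6 |
|---|---|---|
| Nothing (A) | 0.00 | 0.00 |
| Baseline use, one arm only (B) | 0.00 | not needed |
| Week-6 use, same in both arms, slope 1 (A) | 0.00 | 0.00 |
| Week-6 use, app arm only, slope 1 (A) | −0.10 | 0.00 |
| Week-6 use, one arm only, slope 0.8 (B) | −0.08 to −0.10 | within 0.01 of 0 |
| Week-6 use, one arm only, slope 1.2 (B) | −0.12 to −0.14 | within 0.01 of 0 |
| Week-6 use, opposite directions, slope 1 (A) | −0.21 | 0.00 |

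The week-6 column assumes that dropouts were seen at week 6. If half of them also miss week 6 (set B), the bias with the week-6 model is about −0.04 (slope 0.8) to −0.06 (slope 1.2). If all of them miss it, the two methods agree and nothing is gained.

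Under random dropout (set A), the standard error falls from 0.208 to 0.199, about 4%.

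**The case against.** The strongest reply is that this is a pilot. Completion and retention are primary and use all randomized participants as denominator. The quantity analysis is called preliminary, and the Discussion acknowledges the limits of pilot efficacy data. A bias of 0.1 SD is small beside a half-width near 0.47 SD, and fuller missing-data rules may sit in an analysis plan not shown here. The point about consequence stands and keeps this from being a major flaw. The last point does not remove it, because the protocol fixes a specific model and a specific missing-visit statement, and the two do not meet.

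Several stronger readings are tempting but not supported:

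- *That quantity is the only efficacy outcome.* Frequency, abstinence, dependence severity and symptoms are exploratory effect outcomes under GEE. Quantity is the only cannabis-use outcome among the secondary ones.
- *That 30% will certainly lack a week-12 quantity.* The Sample Size section gives 30% as a maximum. Attrition counts anyone who does not complete all week-12 assessments, and visits may be remote, so missing quantity could be lower.
- *That the estimate will be biased.* It is not if dropout is random or depends only on baseline use and arm, and the table shows no bias when dependence on week-6 use is equal in both arms.
- *That the missing-visit statement is false.* Read literally, it is limited to mixed and GEE models. The fault is that it leaves the ANCOVA uncovered. The intention-to-treat sentence is likewise plan-wide and not tied to this model.
- *That the 5% rule would discard the outcome.* It is optional and concerns fields, separately from missed visits.
- *That unweighted GEE is valid only under completely random dropout.* Missingness may also depend on covariates in the model.

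**Conclusion.** The point holds in limited form and is worth acting on. As written, the analysis of cannabis quantity includes only participants with a week-12 value: about 70 of 100 if attrition reaches 30%. Neither the missing-visit statement nor the imputation rule below 5% reaches it. It is therefore a completers' estimate within a plan that announces intention-to-treat analysis.

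The size of any bias is unknown. Roughly 0.1 SD is a reasonable illustration if heavier week-6 use drives dropout in one arm only, and about 0.2 SD if the dependence runs in opposite directions. Both rest on assumed correlations and dropout slopes. In the scenarios tested, the model using week 6 was never materially worse on bias. How far it helps depends on how many dropouts attend week 6, for which the document gives no figure. The primary outcomes are unaffected.

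**What to change.** 1. Analyse quantity with a likelihood-based repeated-measures model on the week-6 and week-12 values: arm by visit, baseline quantity by visit, and sex as the stratification factor. Take the week-12 arm contrast as the estimate. Multiple imputation that includes week 6 is an acceptable alternative.
2. Keep the complete-case ANCOVA as a sensitivity analysis, labelled as completers.
3. Reword the missing-visit statement so that it does not imply protection for the ANCOVA, and say which participants enter each analysis.
4. Add week 6 to the exploratory GEE models.
5. State that the 5% field rules do not apply to outcomes.

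The cost is a change of wording and slightly more programming. No new data are needed. The benefit falls to the extent that those who miss week 12 have also missed week 6, so the report should tabulate attendance at both visits by arm.
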